## Abstract

**Introduction::**

Whether there is the long-term effect of acupuncture on patients with knee osteoarthritis (KOA) or not is controversial. According to the basic theory of traditional acupuncture, *deqi* is the key to the efficacy of acupuncture. This randomized controlled trial aims to evaluate the existence of long-term effects caused by *deqi* in patients with KOA.

**Methods and analysis::**

A three-armed, parallel-design, randomized controlled trial is underway in China.108 KOA patients recruited by the rehabilitation center of the First Affiliated Hospital of Henan University of Traditional Chinese Medicine will be randomly assigned to the acupuncture with *deqi* group (A group), the acupuncture without *deqi* group (B group) and the waiting-list group (C group). Each patient will receive 5 30-minute sessions per week for 4 consecutive weeks and rest for 2 days between treatments, and undergo a 20-week follow-up. The primary outcome is the Western Ontario and McMaster Universities Osteoarthritis index (WOMAC score). The secondary outcomes include Western Ontario and McMaster Universities Osteoarthritis index (WOMAC score), Knee Injury and Osteoarthritis Outcome Score (KOOS), arthritis quality of life measurement scale simplified scale (AIMS2-SF), emotional monitoring and expectation scale. The pain visual analogue scale (VAS) and the Chinese version of modified Massachusetts General Hospital Acupuncture Sensation Scale (C-MMASS) will be used to evaluate the *deqi* sensation after each acupuncture treatment. At the same time, adverse events (AEs) occurred in the whole process will be recorded and analyzed. We will perform an intention-to-treat analysis and protocol (PP) analysis to statistically analyze the results of the trial.

**Discussion::**

This trial will be useful to study the long-term effect of acupuncture and the influence of the *deqi* sensation on the long-term in the treatment of KOA, and to provide a clinical basis for treatment of patients with mild to moderate knee osteoarthritis in clinic.

**Trial registration::**

Chinese Clinical Trial Registry, IDF: ChiCTR2000029291. Registered on January 21, 2020.

## Introduction

1

Knee osteoarthritis, also known as degenerative arthritis or osteoarthritis, is a common clinical disease and high incidence, and is one of the most common diseases in middle-aged and elderly people.^[1]^ Chronic pain is a common clinical symptom of KOA,^[2]^ which seriously reduces the quality of life of patients and is likely to cause other life dysfunction. In severe cases, it even loses joint function and seriously affects the normal life and work of patients. It has become a public health issue of increasing concern in an aging society around the world. Among the reasons for the loss of labor in Europe and the United States, KOA is ranked 4th in women and 8th in men^[3]^ respectively. Among them, over 9 million adults in the United States have KOA, and this prevalence is increasing year by year.^[4]^ A study in China showed that the prevalence of KOA was 33.3% in people over 40 years old, 39.4% in those over 60 years old, and 45.7% in those over 70 years old.^[5]^ But there is no especially effective treatment for KOA. Approximately one-third of direct osteoarthritis expenditures were from medications, mainly for pain-related agents.^[6]^ Currently, most of the clinically targeted drugs for KOA are non-steroidal anti-inflammatory drugs (NSAIDs) and COX-2 selective agents, they are associated with an increased risk of gastrointestinal bleeding and cardiovascular events.^[7]^ And according to multiple research studies, acupuncture has a good therapeutic efficacy on bone impediments, including KOA.^[8–10]^ A number of studies have proven that acupuncture is very effective in the treatment of KOA.^[11,12]^ One systematic review evaluated that acupuncture was shown to be effective for pain control in KOA in sham-controlled RCTs.^[11]^ In the Cochrane review, researchers found that acupuncture had statistically significant and clinically relevant benefits in the treatment of patients with peripheral OA in the waiting list-controlled trials.^[12]^ As a result, considering the short-term analgesic effect and worrying side effects of drugs, more and more people are choosing supplemental replacement therapy with better sustained analgesic effect to treat KOA, and acupuncture is an important tool.

*Deqi*, the ancient name is “*qi* arrival”, also known as “needle sense”, refers to the needle into the acupoints a certain depth, after applying a certain needle-handling method, so that the acupuncture site obtains the induction of *qi*. *Deqi* is the key to the effectiveness of acupuncture and is the basis for the long-term analgesic effect of acupuncture. The long-term effect is the therapeutic effect that still exists after the completion of acupuncture treatment, and is the accumulation and continuation of the immediate effect of acupuncture. The long-term effect has been reported in trials of acupuncture for treating chronic tension-type headache,^[13]^ migraine,^[14]^ primary insomnia,^[15]^ tinnitus,^[16]^ etc. However, the long-term effect of acupuncture on KOA has not been confirmed, so we design a randomized controlled trial (RCT) with a treatment period of 4 weeks and an observation period of 20 weeks to investigate and evaluate the long-term effect of acupuncture for KOA.

## Methods

2

### Study design and registration

2.1

This is a parallel-design, randomized controlled trial comparing the therapeutic outcomes of the acupuncture with *deqi* group, the acupuncture without *deqi* group and the waiting-list group. And this trial belongs to the clinical randomized controlled study, which aims to compare the long-term effect of acupuncture treatment among the 3 groups. This trial will be carried out at the Rehabilitation Center of the First Affiliated Hospital of Henan University of Traditional Chinese Medicine, Zhengzhou, Henan, China. The procedure will last for 24 weeks, including a 4-week treatment and a follow-up period of 20 weeks. Patients in *deqi* group and without *deqi* group will receive 20 sessions of acupuncture during the 4-week treatment. The Figure 1 shows the study design in the flowchart, and the Figure 3 illustrates the time schedule of enrolment, interventions, assessments, and visits of participants. The reporting of this trial is conducted according to the Standard Protocol Items: Recommendations for Intervention Trials (SPIRIT) guidelines (Additional file 1).

**Figure 1 F1:**
[figure not shown]
Flow chart of the trial.

This protocol has been registered in the Chinese Clinical Trial Registry on January 21, 2020, http://www.chictr.org.cn/edit.aspx?pid=38787&htm=4. And the registration number is ChiCTR2000029291.

### Participants

2.2

#### Inclusion criteria

2.2.1

① male or female, aged 45 to 75 years; ② Diagnosis of knee osteoarthritis according to the American College of Rheumatology (ACR) criteria;^[17]^ ③ Radiologic confirmation of knee osteoarthritis (Kellgren–Lawrence grade I or III); ④ the average daily pain over 40 points (on a 0-to 100-point scale); ⑤ written consent to participate in the trial.

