### Sample size

2.3

PASS was used for sample size determination. According to the previous study, WOMAC Function Score of KOA patients decreased by 12.1 points after acupuncture, by 9.4 points after sham acupuncture and 5.6 points after education, while WOMAC pain Score of KOA patients decreased by 3.6 points after acupuncture, by 2.6 points after sham acupuncture and 1.5 points after education.^[18]^ Based on the previous study and our clinical experience, we anticipated a reduction of WOMAC total score by 17 points after acupuncture with the *deqi* sensation, a reduction by 13 points after acupuncture without the *deqi* sensation and a reduction by 8 points in the wait-list control. With α = 0.05, 1 – β = 0.9, and a standard deviation of 10, we need at least 99 participants in total. Considering a dropout rate of 10%, a total of 108 participants will be included in this trial.

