1.Recruitment of middle-aged and elderly patients with mild to moderate recurrent knee pain in the past month to avoid the impact of other diseases on pain assessment;2.In order to alleviate patients doubts about different interventions, patients in each group will be treated in different rooms, and patients in each group will be forbidden to talk.3.The acupuncturist is a doctor with more than 6 years of work experience and a medical practitioner certificate. Relevant personnel and data evaluators responsible for recruiting patients are required to undergo rigorous training before the study to ensure that all experimental procedures have uniform standards and avoid observational bias.4.Emotion monitoring. During the whole study, not only the emotional changes of patients will be evaluated on time by the emotion monitoring scales, but also the emotional changes of each patient should be paid close attention in order to eliminate the influence of emotional changes on the disease.

Of course, this study also has some shortcomings, mainly reflected in the following 2 aspects:

1.Because this study has a long observation period, it will result in a higher rate of abscission, which will affect the results of the study. Therefore, we should maintain a good doctor-patient relationship with patients during the study, and the part of the scales involved in this study are self-rating scale, which can be carried out subjectively by patients to better improve the quality of studys data;2.The patients enrolled in this study are limited to mild to moderate KOA patients, so the results of this study have some limitations, they may only be applicable to mild to moderate KOA individuals.

Most domestic and international medical treatment guidelines recommend acupuncture for knee osteoarthritis, but the long-term effect of acupuncture for KOA is not fully defined. Therefore, this study designs a clinical study with a treatment period of 4 weeks and a follow-up period of 20 weeks, aiming to study the long-term effect of acupuncture and the influence of the *deqi* sensation on the long-term in the treatment of KOA, and to provide a clinical basis for treatment of patients with mild to moderate knee osteoarthritis in clinic.

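### The radiographic inclusion criterion names Kellgren–Lawrence grades I and III but not II, which does not fit the stated mild to moderate population; the intended grades must be confirmed and stated

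*Protocol article*

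**What the plan says.** Protocol article, section 2.2.1 (Inclusion criteria), third criterion: "Radiologic confirmation of knee osteoarthritis (Kellgren–Lawrence grade I or III". This is the only inclusion criterion that grades structural disease, and no other part of the article shown names a Kellgren–Lawrence grade.

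The article describes its population in three other places:

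- The Discussion paragraph of the Abstract says the trial is meant "to provide a clinical basis for treatment of patients with mild to moderate knee osteoarthritis in clinic".
- The shortcomings in section 5 say "The patients enrolled in this study are limited to mild to moderate KOA patients" and, of the results, that "they may only be applicable to mild to moderate KOA individuals".
- The quality-control list in section 5 refers to "Recruitment of middle-aged and elderly patients with mild to moderate recurrent knee pain in the past month". This describes symptoms, not radiographic severity.

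Section 6 (Trial status) gives protocol version V1.0 and says that recruitment began on March 1, 2020 and was still under way.

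**The concern.** Kellgren–Lawrence grades are ordered, so grade II lies between I and III. A criterion that lists I and III joined by *or* names two separate grades, not a span. Taken as written, it leaves a hole inside its own range. A population described simply as mild to moderate has no such hole.

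The line decides who enters the trial, so the uncertainty matters whichever way it is handled:

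- **If followed literally**, grade II patients are screen failures. The sample consists of two non-adjacent grades, and a conclusion about mild to moderate disease does not describe who was studied.
- **If read by staff as something else**, any grade II patient enrolled breaches the published criterion. A reader of the final report cannot tell from the article which patients were meant to be eligible.

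**Working it through.** No arithmetic decides this point. The check sets the criterion beside the rest of the article, then tests whether the trial's own figures depend on it.

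**Step 1. Does anything explain or repair the gap?**

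- Exclusion criteria (2.2.2): none removes grade II, and none mentions a radiographic grade.
- Pain criterion (2.2.1): "the average daily pain over 40 points (on a 0-to 100-point scale". It sets a floor with no upper limit and says nothing about structural grade, so it does not define the mild to moderate range either.
- Introduction and section 5: no rationale for studying two non-adjacent grades.

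**Step 2. Do the possible readings differ in substance?** These are illustrations, and none is put forward as the right one.

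| Reading of criterion 3 | Grade I | Grade II | Grade III |
|---|---|---|---|
| Literal: I or III | eligible | not eligible | eligible |
| A range from I to III | eligible | eligible | eligible |
| Two adjacent grades, II and III | not eligible | eligible | eligible |
| Two adjacent grades, I and II | eligible | eligible | not eligible |

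The four readings give four different populations. Each of the three alternatives admits grade II, but they disagree on grade I or grade III. A reader who assumes a slip still does not know who is eligible.

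**Step 3. Does the sample size depend on grade?** Section 2.3 assumes falls in the WOMAC total of 17 (*deqi* arm), 13 (arm without *deqi*) and 8 (waiting list), with SD 10, α = 0.05 and power 0.90. It does not name the test. A one-way ANOVA F test with three equal arms reproduces its figure:

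- Mean of the three reductions: (17 + 13 + 8)/3 = 12.667.
- Sum of squared deviations: 4.333² + 0.333² + (−4.667)² = 18.78 + 0.11 + 21.78 = 40.67.
- Noncentrality at n per arm: n × 40.67/10² = 0.4067n, which is 13.42 at n = 33.
- Power is 0.908 at 33 per arm (N = 99) and 0.899 at 32 per arm (N = 96).

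So 99 is the smallest equal-arm total that reaches 0.90, as stated. For 10% dropout, 99 × 1.1 = 108.9 and 99/0.9 = 110; the stated 108 is close to both. No input refers to radiographic grade.

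**Step 4. Does the comparison depend on grade?** Allocation is 1:1:1 by simple randomization (2.4), and the repeated measures ANOVA compares the three groups (4.6). Grade enters neither. Whichever grades are admitted, the arms are compared within the same randomised set of patients.

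**Step 5. Can the effect on recruitment be sized?** If a share p of otherwise eligible patients is grade II, excluding them multiplies the screening needed by 1/(1 − p). The article gives no value for p and no data on screening or grade distribution, so the factor cannot be evaluated.

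**The case against.** The strongest reply is that this is a typographical slip in a condensed article. The printed text is one character away from naming II and III, and one word away from a range. Nothing in the article argues for omitting grade II, and a character lost in typesetting or text extraction cannot be ruled out, although nothing shows that one was. The possibility of a slip stands. It does not dispose of the point, because the plausible corrections admit different patients (Step 2) and the article does not choose between them.

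A second reply is that the conflict with the stated population is looser than it looks. The article never maps grades to mild or moderate, one of its uses of the phrase concerns pain, and the sentence on applicability is a hedged outer limit. All of this is correct. That grade II is intermediate rests on the ordering alone. The Abstract's statement of clinical purpose and the section 5 statement about who is enrolled still describe disease severity as an unbroken range.

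Three stronger inferences are tempting, and the documents support none of them:

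- *That the sites are screening out grade II patients.* Section 6 shows that recruitment is under way. The full protocol V1.0 and the screening forms are not shown, so the grades staff apply are unknown.
- *That recruitment must rise by some stated factor.* Any such factor restates a guess at p, and the article reports no recruitment shortfall.
- *That the treatment comparison is biased or underpowered.* Steps 3 and 4 show no route by which grade enters either.

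**Conclusion.** The criterion is wrong as written. It literally excludes an intermediate grade without explanation, and it does not fit the mild to moderate population that the article says is enrolled and will be described by the results. This holds on the text alone and needs only the ordering of the grades.

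The consequence is limited to clarity of eligibility and generalisability. It has no numerical size that can be derived from the article. The randomised comparison, the 99 evaluable patients and the 108 to be enrolled are unaffected. Whether the literal rule has been applied, or only misprinted, is open until the full protocol and screening forms are checked. Correction is worthwhile because the line decides who is screened in and the repair is cheap.

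**What to change.** 1. The sponsor checks criterion 3 in the full protocol and on the screening forms, and establishes which grades have been applied.
2. The sponsor reconciles criterion 3 with the stated population and lists every admitted grade explicitly. The choice of grades is a clinical decision for the sponsor.
3. If only the article is wrong, a published correction is enough. If the operative criterion is wrong, it is changed by protocol amendment, with the date recorded.
4. The grade is recorded at screening. The final report gives the number enrolled by grade and, if there is an amendment, separately before and after it.
5. The conclusion is limited to the grades actually studied.

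The cost is a one-line text change, one recorded item at screening and one table row in the report. A correction to the article alone has no consequence for the analysis. An amendment made during recruitment would change the mix of patients from that date, which is why the counts before and after are needed.

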#### Exclusion criteria

2.2.2

Subjects will be excluded if they meet any of the following criteria: ① are unable to walk; ② have a serious infection of the knee; ③ have suspected tears in any ligaments or menisci or acute inflammation of the synovial capsule; ④ have a history of trauma, ligament damage, fracture, or surgery on the knee(s) within 6 months, causing pain or functional problems (history of knee replacement will be excluded); ⑤ have a history of local tumor/malignancy at the knee; ⑥ have physical or laboratory findings indicating infection, presence of autoimmune disease or inflammatory arthritis; ⑦ have knee pain caused by radiculopathy/herniation of an intervertebral disc; ⑧ have end-stage diseases or other suspected severe conditions such as deep vein thrombosis of the lower limb, oedema related to cancer or cancer treatment, severe blood coagulation disorders, uncontrolled systemic arterial hypertension and severe diabetes; ⑨ have a history of prolotherapy, hyaluronic acid injections or corticosteroids injections within 3 months; 

 have received acupuncture, electro-acupuncture, Tui-na therapy, massage, or physiotherapy 8 weeks prior to enrolment in the trial; 

 have severe pain in other regions; 

 have severe mental disorder(s); 

 are oversensitive to needles; and 

 are insensitive to pain due to advanced diabetes, neuropathy or use of strong painkillers.

### Sample size

2.3

PASS was used for sample size determination. According to the previous study, WOMAC Function Score of KOA patients decreased by 12.1 points after acupuncture, by 9.4 points after sham acupuncture and 5.6 points after education, while WOMAC pain Score of KOA patients decreased by 3.6 points after acupuncture, by 2.6 points after sham acupuncture and 1.5 points after education.^[18]^ Based on the previous study and our clinical experience, we anticipated a reduction of WOMAC total score by 17 points after acupuncture with the *deqi* sensation, a reduction by 13 points after acupuncture without the *deqi* sensation and a reduction by 8 points in the wait-list control. With α = 0.05, 1 – β = 0.9, and a standard deviation of 10, we need at least 99 participants in total. Considering a dropout rate of 10%, a total of 108 participants will be included in this trial.

### Randomization

2.4

Patients who meet the inclusion criteria will be randomly assigned to 3 groups of the trial in a ratio of 1:1:1 by a third party using simple concealed randomization to avoid possible selection bias. And the random assignment protocol will be generated by the third party who will not participate in the trial and use the PROCPLAN process of the SAS package. At 5 to 10 minutes prior to the acupuncture treatment, the acupuncturist will inform the manager of the randomization program about the patient number and name via telephone; the acupuncturist will then be informed of the patients randomization number and treatment group. The randomization information will be concealed in the server until the end of the trial.

### Blinding

2.5

The acupuncturist and patients will not be blinded because of the nature of the intervention. However, it is feasible to conceal the researchers, statisticians and the outcome assessors. The outcome assessor and data analyst will be blinded to group assignments. Unblinding will not be done until the completion of data analysis, and after the data analysis, we will have blinded interpretation of the study results to minimize misleading data interpretation additional file 1.

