### Evaluation indexes of *deq*i

4.3

Before the acupuncture treatment, each patient will be introduced with the concept of *deqi* and the sensation of *deqi*. Participants in the acupuncture with the *deqi* group and acupuncture without the *deqi* group will be asked to fill the needle sensation evaluation form after receiving each acupuncture treatment.

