The randomized controlled study design is an in-depth study of reliable methods based on the long-term analgesic effect of acupuncture. At the same time, it is a randomized controlled study that is an important source of high-quality evidence-based medical evidence for acupuncture. In the trial, we take acupuncture without *deqi* group as the control group. It is often regarded as a sham control group, because its acupuncture depth is only broken and does not reach the anatomical layer of the acupuncture point. Studies^[42–44]^ have shown that the placebo effect of sham acupuncture is more pronounced than drug-based placebo, especially for subjective outcomes and pain management. Therefore, our study has set a sham acupuncture group to eliminate the effects of placebo effects and patients’ expectations. And in the idea of acupuncture treatment of knee osteoarthritis, local acupoints have been used since ancient times. “*Su Wen*” says, local *Ashi* Point for the treatment of knee pain. A number of modern clinical studies^[44,45]^ have shown that local acupoints are widely used in the treatment of KOA by acupuncture, and the curative effect is remarkable. Some researchers^[45]^ used data mining to analyze the relevant literature of modern acupuncture treatment for KOA, and found that *Dubi*, *Neixiyan* and *Yanglingquan* were the top 3 acupoints with the high frequency. Another study^[46]^ shows that *Ashi* point is also one of the high-frequency acupoints. Thus, this study will select *Dubi*, *Neixiyan* and *Yanglingquan*, *Yinlingquan* as the acupuncture points. At the same time, depending on the patient's condition, 2 local acupuncture points can be added.

In order to improve the reliability of the study data, we carry out quality control from the following aspects:

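### The Discussion says the shallow-needling arm eliminates placebo and expectation effects, but patients are unblinded, so an A versus B difference cannot be credited to deqi alone

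*Protocol article*

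**What the plan says.** Section 2.5 (Blinding) leaves patients and the acupuncturist open: "The acupuncturist and patients will not be blinded because of the nature of the intervention". It adds that "The outcome assessor and data analyst will be blinded to group assignments".

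Section 5 (Discussion) says of the arm without deqi: "It is often regarded as a sham control group". It then gives the arm's purpose: "our study has set a sham acupuncture group to eliminate the effects of placebo effects and patients’ expectations".

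Section 4.3 (Evaluation indexes of deqi) says that before treatment "each patient will be introduced with the concept of" deqi and to its sensation. Patients in the two needling arms "will be asked to fill the needle sensation evaluation form after receiving each acupuncture treatment". Section 2.1 sets 20 sessions.

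Section 3.2 has group B needled at 1–2 mm, with 30 minutes' retention and no manipulation, so as to avoid deqi as far as possible. Section 3.1 has group A needled with manipulation, repeated during retention, to obtain and keep the sensation.

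Three other places bear on expectation:
- Section 4.2.5 asks one expectancy question, about acupuncture therapy in general, at the first visit.
- The quality-control list in section 5 treats the groups in separate rooms and forbids patients to talk.
- The limitations in section 5 are two: loss to follow-up, and restriction to mild to moderate disease. Unblinded patients are not listed.

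**The concern.** A sham arm controls expectation only to the extent that patients cannot tell which treatment they are receiving. Section 2.5 says they are not blinded, and section 5 claims the property that blinding would have supplied. As written, the design does not have that property for A versus B.

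This contrast carries the trial's stated aim. The Abstract sets out to evaluate long-term effects caused by deqi, and only A versus B separates needling with deqi from needling without it. The comparison of A with the waiting list mixes deqi with everything else that comes with being treated.

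If patients in A expect more and patients in B are disappointed, WOMAC at week 16 could differ between the arms without any effect of deqi itself. A reader who relies on the Discussion would think this explanation had been ruled out.

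**Working it through.** **1. The passages side by side**

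| Question | What the document gives | Consequence for A versus B |
|---|---|---|
| Do patients know their arm? | Not blinded (2.5) | Expectation can differ by arm |
| Do patients know what deqi feels like? | Each is introduced to it before treatment (4.3) | B patients may notice its absence |
| Is attention drawn to it again? | Form after each session (4.3), 20 sessions (2.1) | Repeated prompt in both arms |
| Are assessor and analyst blinded? | Yes (2.5) | Guards against observer bias, not against a patient's own answers |
| Is expectancy measured? | Once, first visit, acupuncture in general (4.2.5) | Cannot show an A-B difference that develops during treatment |
| Separate rooms, no talking? | Yes (5) | Limits contact between patients; does not conceal the arm |
| What does B share with A? | Same procedures apart from depth and manipulation (3.2), 20 sessions (2.1), same acupuncturist (2.6) | Contact, ritual and attention are balanced |

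The last row is what group B does deliver. No row delivers equal expectation.

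**2. Is WOMAC reported by the patient?** Section 4.1 describes 24 items on pain, stiffness and physical function. Section 4.2.2 says KOOS is completed by the patient. Section 5 says only that part of the scales are self-rated and does not name WOMAC. That WOMAC rests on the patient's report is therefore an inference from its content, and it holds whoever writes the answers down.

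**3. The plan's own figure.** Inputs from section 2.3: reductions of 17, 13 and 8 points, SD 10, α = 0.05, power 0.9; three equal arms from section 2.4.
- Mean reduction = (17 + 13 + 8)/3 = 12.67. Sum of squared deviations = 18.78 + 0.11 + 21.78 = 40.67.
- Noncentrality for the one-way ANOVA F test with n per arm = n × 40.67/100. At n = 33 it is 13.42.
- Power is 0.899 at 32 per arm and 0.908 at 33 per arm, so the stated 99 in total is reproduced. This point does not affect it.

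**4. Size of the contrast at risk.** A-B = 17 − 13 = 4 points; 4/10 = 0.4 SD.

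**5. Illustration only.** The documents give no size for expectation bias, so a range of 1 to 4 points (0.1 to 0.4 SD) in favour of A is assumed, with no true effect of deqi. The chance that a two-sided 5% A-B comparison is significant is Φ(b/SE − 1.96) + Φ(−b/SE − 1.96), with SE = 10 × √(2/n). At n = 33, SE = 2.46.

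| Assumed bias b (points) | 33 per arm | 36 per arm |
|---|---|---|
| 0 | 5% | 5% |
| 1 | 7% | 7% |
| 2 | 13% | 14% |
| 3 | 23% | 25% |
| 4 | 37% | 40% |

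The 33 and 36 per arm are 99/3 and 108/3. In this comparison a 4-point bias behaves exactly like the planned 4-point effect, and nothing measured after the first visit under the present plan would help to tell them apart.

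**The case against.** The best defence is that the fault lies in one word. Group B differs from A in depth and manipulation but otherwise has the same procedures, retention time, number of sessions and acupuncturist. Even unblinded, it removes much of what an untreated control would leave in. That stands: a reader might infer that an open sham arm controls nothing, and the document does not support this.

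The introduction to deqi and the sensation forms also have a legitimate purpose, which is to check that the two arms really differ in deqi. Section 4.3 does not say patients are told that deqi is needed for benefit, and section 3.2 avoids it only as far as possible. It is therefore plausible, but not established, that group B patients will conclude they are missing something.

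A reader might also infer that A and B could plainly have been blinded, because both receive retained needles. The document does not show this. Manipulated and shallow unmanipulated needling may feel different, acupuncture is an exclusion only within the 8 weeks before enrolment (section 2.2.2), and the C-MMASS lists 11 sensations after every session. Declaring patients unblinded is a defensible choice. Recruitment began on March 1, 2020 (section 6), so changing patient information now would mix patients informed in two ways.

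None of this rescues the claim in section 5. If blinding is not attainable, the claim that expectation is eliminated has to go.

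**Conclusion.** The point holds as a conflict between sections 2.5 and 5. The plan claims for group B a property that unblinded allocation cannot give it, and the single expectancy item, the separate rooms and the ban on talking do not restore it. Group B balances contact and procedure, not expectation. A difference between A and B would therefore be the combined effect of deqi and any difference in expectation.

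The amount of bias is unknown. The only firm figure is the planned gap of 4 points (0.4 SD), which leaves little room for bias before the reading changes. A reader might infer from the illustration that expectation accounts for a quarter or more of the planned effect. That would be wrong: the 1 to 4 points are assumed, and the upper end was set equal to the planned effect.

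The conclusion rests on two assumptions: that WOMAC answers come from the patient, and that unblinded patients in A and B may come to hold different expectations. It does not touch the sample size.

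**What to change.** **Text, for the whole trial.** In section 5, replace the elimination claim with a statement that group B balances contact and procedure but not expectation. Add unblinded patients to the limitations. In the report, do not attribute an A-B difference to deqi alone. This costs only wording.

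**Patients not yet enrolled.** Use a neutral introduction to the sensation form, identical in A and B, and where feasible do not disclose which needling style is given. The waiting list stays open.

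**Week 4.** Ask patients in A and B which style they think they received, and repeat the expectancy item of section 4.2.5. Report the A-B result alongside these answers and by whether the patient enrolled before or after the change.

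**Cost.** An ethics amendment, revised patient information and two extra questions. Blinding may be imperfect, which is why the guess is needed. Each needling arm will hold patients informed before and after the change, so the split by enrolment date has to be reported. If recruitment is too far advanced for the amendment, the text changes should still be made.
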